### 6.3.4 The appropriateness or inappropriateness of hospitalizations

The analysis will compare the risk of "inappropriate" or "avoidable" admission to a hospital ward (including emergencies) within 18 months of follow-up between the two groups using a mixed logistic regression model. The randomization group will be considered a fixed effect and the center as a random effect.

### 6.3.5 The prevalence of psycho-behavioral disorders

The total score obtained in the NPI version for the nursing team at the end-of-study visit will be compared between the 2 groups using a mixed model of analysis of variance (comparison of mean values). The randomization group will be considered as a fixed effect and the center as a random effect.

### 6.3.6 The residents' process of entry into the dependency

The difference between the GIR scores at the end-of-study visit and during the inclusion visit will be compared between the 2 groups using a mixed model of covariance analysis (comparison of mean values by adjusting for the inclusion score). The randomization group and the inclusion score will be considered as fixed effects and the center as a random effect. The total score obtained on the 4 items of the Lawton IADL at the end-of-study visit will be compared between the 2 groups using a mixed model of analysis of variance (comparison of

|                    |                                                                   |                                                                                                            |
|--------------------|-------------------------------------------------------------------|------------------------------------------------------------------------------------------------------------|
| Principal analysis | Statistical Analysis Plan (SAP)-IDEM Study 0910701
Version 1.0 | [figure not shown]
Hôpitaux de Toulouse |
|                    |                                                                   | 07/22/2016                                                                                                 |

mean values). The randomization group will be considered as a fixed effect and the center as a random effect.

### 6.3.7 The residents' quality of life

The total score obtained by the QOL-AD scale at the end-of-study visit will be compared between the 2 groups using a mixed model of analysis of variance (comparison of mean values). The randomization group will be considered as a fixed effect and the center as a random effect.

### 6.3.8 The burden of the NH staff

This analysis will be done at the center level and not at the subject level. The total number of work interruptions and the number of cumulative days reported per 100 residents registered during the study duration in each EHPAD center will be compared between the 2 groups using a Student's test to compare the mean values (Two- Sample T-test).

Population of analysis: These analyzes will be made **on the population of randomized NHs**.

### 6.3.9 The advanced care planning measures (advance directives ...)

The presence of prescriptions in the residents' file at the end of the study will be compared between the 2 groups using a mixed model of logistic regression. The randomization group will be considered as a fixed effect and the center as a random effect.

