Note 2: The number of beds / residents in each NH will be used as a measure of the number of caregivers working in each NH. Indeed, the number of NH caregivers is counted according to the number of residents / beds. Thus, the number of work interruptions in each NH will be transformed into the number of interruptions per 100 beds / residents in order to be compared between the centers.

Note 3: The turnover and the departures of the caregivers, were not collected.

g- The advanced care planning measures (advance directives ...)

|                    |                                                                   |                                                                                                            |
|--------------------|-------------------------------------------------------------------|------------------------------------------------------------------------------------------------------------|
| Principal analysis | Statistical Analysis Plan (SAP)-IDEM Study 0910701
Version 1.0 | [figure not shown]
Hôpitaux de Toulouse |
|                    |                                                                   | 07/22/2016                                                                                                 |

The endpoint will be the addition of at least one advance directive, whatever the type, in the resident's file during the 18 months of follow-up. The additions will be analyzed first globally then separately for each type of advance directive defined below.

Here are the 10 items collected in the CRF for the two intervention and control groups concerning "The planning of specific therapeutic measures" (advance directives):

- Prescriptions of therapeutic drug protocols for the management of behavioral disorders
- Requirements for non-drug therapeutic protocols for the management of behavioral disorders
- Prescriptions of therapeutic drug protocols for the management of pain
- Prescriptions of therapeutic drug protocols for the management of end-of-life discomfort symptoms (other than pain)
- Requirements for non-medical therapeutic protocols for the management of end-of-life discomfort symptoms (other than pain)
- No transfer in intensive care
- No transfer to ED
- No resuscitation
- No hospitalization
- Other

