## 6.5 Descriptive analyzes

### 6.5.1 General

Additional descriptive analyzes will be produced on the inclusion data as well as data collected during the study that are not the endpoints. The quantitative variables will be summarized by their mean, standard deviation, median, 1st and 3rd quartile (Q1 and Q3), minimum and maximum. For qualitative variables, the number and percentage corresponding to each category will be presented.

Descriptions will be performed by randomization group of the subjects' NH and in total. The differences between the 2 groups will not be tested statistically in these descriptive analyzes.

Population of analysis: The descriptive analyzes will be done **on the subjects of the ITT population for which the data is available**, except if another population is defined explicitly.

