### 6.5.3 Description of data collected at inclusion

The characteristics found in the randomized NH centers (randomization stratification factors, number of residents included) will first be described.

The following characteristics of the subjects identified for inclusion in the study will be described for the entire analysis population and will be described in the 2 groups (intervention, control):

- Criteria for inclusion and non-inclusion;
- Sociodemographic characteristics (age, sex, marital status, education, mother tongue (French yes / no), occupation (yes / no), seniority in the NH (in months);
- Medical history and associated pathologies (visual or auditory impairment, smoking and alcohol consumption, total Charlson Comorbidity Index score);

|                    |                                                                   |                                                                                                            |
|--------------------|-------------------------------------------------------------------|------------------------------------------------------------------------------------------------------------|
| Principal analysis | Statistical Analysis Plan (SAP)-IDEM Study 0910701
Version 1.0 | [figure not shown]
Hôpitaux de Toulouse |
|                    |                                                                   | 07/22/2016                                                                                                 |

- Cognitive antecedents (progressive decline yes / no, MMSE test yes / no and score, cognitive assessments yes / no and type of assessment);
- Family history of dementia (presence of family history of dementia yes / no);
- Hospitalizations during the last 3 months by type of hospitalization (planned or in emergency) and by type of service;
- Ongoing drug and non-drug treatments at inclusion by type of treatment;
- Anticipated prescriptions by type;
- GIR total score at inclusion.

The following results from the Comprehensive Geriatric Assessment (CGA) obtained during the inclusion visit only for the intervention group, will be described:

- Overall MMSE score;
- Results of the clock test (score and normality);
- Results of the Borson Mini-Cog (normality);
- Overall score of the 5 word test;
- Categorical verbal fluency test results (total words generated, total acceptable words);
- Confusion Assessment Method (CAM) test result (acute confusional state yes / no);

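### The advance-directive endpoint is an addition during follow-up (SAP 4.2 g), but the planned model (6.3.9) analyses presence on file at study end, which is a different variable

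*SAP*

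**What the plan says.** Section 4.2 g sets the endpoint as "the addition of at least one advance directive, whatever the type, in the resident's file during the 18 months of follow-up". It continues: "The additions will be analyzed first globally then separately for each type of advance directive defined below". It then lists ten items, recorded in both arms ("Here are the 10 items collected in the CRF for the two intervention and control groups").

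Section 6.3.9, the analysis section for this endpoint, says: "The presence of prescriptions in the residents' file at the end of the study will be compared between the 2 groups". The method is a mixed logistic regression, and its terms are given in full: "The randomization group will be considered as a fixed effect and the center as a random effect". There is no term for status at inclusion, no restriction to residents without a directive at inclusion, and no mention of the analyses by type.

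Status at inclusion is recorded. Section 6.5.3 lists "Anticipated prescriptions by type" among the characteristics to be described in both groups. Section 6.5.1 limits such data to description: "The differences between the 2 groups will not be tested statistically in these descriptive analyzes".

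Section 2, on changes from the protocol, mentions only the loss of blinding of the analysis. It does not mention a switch from addition to presence.

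**The concern.** An addition over a period and presence at a time point are two different binary variables. They disagree in at least three situations:

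- **A directive on file at inclusion and none added.** Presence is yes, addition is no.
- **A directive on file at inclusion and another type added.** Addition is yes, because 4.2 g counts any type. Overall presence is yes whether or not the new one was added, so the gain cannot be seen.
- **A directive added, after which the resident dies or leaves.** Addition is yes. Presence at study end has no stated definition for this resident.

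The analyst therefore has two instructions for one endpoint and must choose between them. Section 2 says the analyses will not be blind, so the choice should be fixed beforehand. The endpoint also has explanatory value. The ten items include directives against transfer to the ED and against hospitalization, and the SAP summary (Expected Outcomes) names advance directives among the elements of the meeting's opinion expected to prevent some hospitalizations.

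**Working it through.** The SAP states no rate, effect size or power for this endpoint, so there is no figure to reproduce. The contradiction rests on the wording above. What follows shows how far the two variables can diverge. All rates are assumptions.

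**Notation.** Let b be the share with a directive at inclusion and a the share of the remainder who gain one. For simplicity, residents who already have one gain no other. Among all residents:

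- addition = (1 − b) × a
- presence at the end = b + (1 − b) × a

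**1. Dilution with equal baselines.** Assume b = 40% in both arms, a = 30% (intervention) and 20% (control).

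- Addition: 0.60 × 0.30 = 18% vs 0.60 × 0.20 = 12%. OR = (0.18/0.82)/(0.12/0.88) = 1.61.
- Presence: 0.40 + 0.18 = 58% vs 0.40 + 0.12 = 52%. OR = (0.58/0.42)/(0.52/0.48) = 1.27.

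The risk difference is 6 points in both cases. The odds ratio, which is what a logistic model estimates, shrinks, and precision falls because presence lies nearer 50%. To size this, take 1,000 per arm and 30 residents per home (SAP 3.3), ignore attrition, and borrow the ICC of 0.02 set there for the primary endpoint, since none is given for directives. The design effect is 1 + 29 × 0.02 = 1.58, so the effective n is 1000/1.58 = 633 per arm. By the normal approximation:

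- Addition: SE = √[(0.18×0.82 + 0.12×0.88)/633] = 0.0200; 0.06/0.0200 = 3.00; power about 85%.
- Presence: SE = √[(0.58×0.42 + 0.52×0.48)/633] = 0.0279; 0.06/0.0279 = 2.15; power about 57%.

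**2. No true effect, equal baselines.** With a = 10% and b = 30% in both arms, presence is 0.30 + 0.70 × 0.10 = 37% in each arm, OR 1.00. Pre-existing directives alone create no effect.

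**3. No true effect, unequal baselines.** With a = 10% in both arms and b = 35% (intervention) vs 25% (control):

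- Presence: 0.35 + 0.065 = 41.5% vs 0.25 + 0.075 = 32.5%, OR 1.47. With the arms reversed, OR 0.68.
- Addition: 6.5% vs 7.5%, OR 0.86. Some imbalance remains, but it is 1 point instead of 9.

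**4. How large a chance imbalance could be.** At an assumed 30% prevalence, 95% range = ±1.96 × √[2 × 0.3 × 0.7/1000 × (1 + 29 × ICC)]:

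| Assumed ICC | Range |
|---|---|
| 0.02 | ±5 points |
| 0.10 | ±8 points |
| 0.30 | ±12.5 points |

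The 10-point gap in step 3 is therefore unlikely at an ICC of 0.02 and plausible only if directives cluster strongly by home. The SAP gives no information on that.

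**5. Residents who leave.** SAP 3.3 assumes 20% attrition, described as yearly deaths. If that rate held for 18 months, 1 − 0.8^1.5 = 28% would be gone by the end. Section 6.3.1 analyses ITT subjects for whom the endpoint is available, and section 7 imputes nothing except incomplete dates. How presence at study end is set for these residents is not stated. Three of the ten items concern end-of-life symptoms or resuscitation, so these residents matter to the endpoint.

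**The case against.** The intended variable is already stated in 4.2 g, and presence in 6.3.9 may be loose wording for the same thing. That is possible, but nothing in 6.3.9 says so. Other change endpoints are analysed as change: 6.3.3 models the modification of non-drug treatment, and 6.3.6 compares the GIR difference adjusted for the inclusion score.

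Chance imbalance between randomized homes is sampling variation, which the random center effect is there to reflect, and omitting a baseline covariate is not in itself an error. This stands. The imbalance argument concerns a noisier estimate in any one trial, not expected bias, and the document shows no actual imbalance.

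Two stronger readings are tempting and neither is supported:

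- **A reader might infer that directives on file at inclusion would be credited to the intervention.** They count in both randomized arms, and with equal baselines and no true effect the odds ratio is 1.00 (step 2). The expected consequence is dilution. A spurious difference needs an imbalance and can go either way.
- **A reader might infer that residents who died are excluded.** Section 6.3.9 refers to the file at the end of the study, not to the end-of-study visit named for the NPI, GIR, IADL and QOL-AD. A file can be checked after a death. The SAP is silent on these residents; it does not leave them out.

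**Conclusion.** The contradiction is real: 4.2 g defines an addition during follow-up, globally and by type, and 6.3.9 models presence at study end. The inclusion data needed to tell them apart are recorded, but 6.3.9 does not use them.

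The expected consequence is a diluted odds ratio and lost precision: 1.61 against 1.27, and about 85% against 57% power, under the assumed rates in step 1. A chance baseline imbalance would also enter the estimate more fully than with addition. These sizes rest on assumed prevalences, assumed addition rates, a borrowed ICC, and the simplification that residents with a directive gain no other. The contradiction itself rests on none of them.

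The severity is moderate. This is one secondary endpoint, section 6.3.1 declares all such tests exploratory, and the primary analysis is unaffected.

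**What to change.** Rewrite 6.3.9 so that the outcome is the addition of at least one directive during the 18 months, derived from the inclusion and follow-up records, with group as fixed effect and center as random effect.

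- **Overall analysis:** ITT residents, counting additions made before death or exit. Having any directive at inclusion may be a covariate here, because residents who have one can still gain another type.
- **By type:** for each of the ten types, residents without that type at inclusion, with no baseline term for that type. If residents who already have the type were kept in and a baseline term added, they could never have the event, and that term would have no finite maximum-likelihood estimate.

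Presence at study end can be kept as description. Alternatively, if presence is what is wanted, amend 4.2 g to say so, state how it is determined for residents who died or left, and adjust for presence at inclusion.

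Either route costs SAP wording and some derivation programming. Inclusion status is already recorded, and the ten items are collected in both arms. It should be settled before the analysis starts.

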## 6.4 Analysis of the additional endpoints

A mixed logistic regression model will be conducted to study the effect of the intervention on the risk of admission to a hospital ward. The effect of the intervention will be tested with a risk of 5% (exploratory test). The incidence rates of hospitalizations over a period of 18 months of follow-up will be calculated in each group.

These analyzes will be carried out **on ITT, PP1 and PP2 populations**.

|                    |                                                                   |                                                                                                            |
|--------------------|-------------------------------------------------------------------|------------------------------------------------------------------------------------------------------------|
| Principal analysis | Statistical Analysis Plan (SAP)-IDEM Study 0910701
Version 1.0 | [figure not shown]
Hôpitaux de Toulouse |
|                    |                                                                   | 07/22/2016                                                                                                 |

## 6.5 Descriptive analyzes

### 6.5.1 General

Additional descriptive analyzes will be produced on the inclusion data as well as data collected during the study that are not the endpoints. The quantitative variables will be summarized by their mean, standard deviation, median, 1st and 3rd quartile (Q1 and Q3), minimum and maximum. For qualitative variables, the number and percentage corresponding to each category will be presented.

Descriptions will be performed by randomization group of the subjects' NH and in total. The differences between the 2 groups will not be tested statistically in these descriptive analyzes.

Population of analysis: The descriptive analyzes will be done **on the subjects of the ITT population for which the data is available**, except if another population is defined explicitly.

### 6.5.2 Description of subjects not included

The number of residents of the randomized NH not included in the study will be described as well as the reasons for not including.

### 6.5.3 Description of data collected at inclusion

The characteristics found in the randomized NH centers (randomization stratification factors, number of residents included) will first be described.

The following characteristics of the subjects identified for inclusion in the study will be described for the entire analysis population and will be described in the 2 groups (intervention, control):

- Criteria for inclusion and non-inclusion;
- Sociodemographic characteristics (age, sex, marital status, education, mother tongue (French yes / no), occupation (yes / no), seniority in the NH (in months);
- Medical history and associated pathologies (visual or auditory impairment, smoking and alcohol consumption, total Charlson Comorbidity Index score);

|                    |                                                                   |                                                                                                            |
|--------------------|-------------------------------------------------------------------|------------------------------------------------------------------------------------------------------------|
| Principal analysis | Statistical Analysis Plan (SAP)-IDEM Study 0910701
Version 1.0 | [figure not shown]
Hôpitaux de Toulouse |
|                    |                                                                   | 07/22/2016                                                                                                 |

- Cognitive antecedents (progressive decline yes / no, MMSE test yes / no and score, cognitive assessments yes / no and type of assessment);
- Family history of dementia (presence of family history of dementia yes / no);
- Hospitalizations during the last 3 months by type of hospitalization (planned or in emergency) and by type of service;
- Ongoing drug and non-drug treatments at inclusion by type of treatment;
- Anticipated prescriptions by type;
- GIR total score at inclusion.

The following results from the Comprehensive Geriatric Assessment (CGA) obtained during the inclusion visit only for the intervention group, will be described:

- Overall MMSE score;
- Results of the clock test (score and normality);
- Results of the Borson Mini-Cog (normality);
- Overall score of the 5 word test;
- Categorical verbal fluency test results (total words generated, total acceptable words);
- Confusion Assessment Method (CAM) test result (acute confusional state yes / no);
- Results of the Mini-Nutritional Assessment (MNA) test (total score, assessment);
- Result of the one-leg standing balance test (normality);
- Neuropsychiatric Inventory (caregiver version) test results (NPI / ES) (total score);
- Result of Mini-GDS (total score);
- Results of the QOL-AD (total score);
- IADL results

Regarding drug treatments, the number and percentage of subjects taking neuroleptics, benzodiazepines, anxiolytics, antidepressants, hypnotics or thymo-regulators at inclusion will be described.

#### **6.5.4 Description of the data collected during the first multidisciplinary team meeting (MDTM1)**

This descriptive analysis concerns the subjects in the intervention group only.

|                    |                                                                   |                                                                                                            |
|--------------------|-------------------------------------------------------------------|------------------------------------------------------------------------------------------------------------|
| Principal analysis | Statistical Analysis Plan (SAP)-IDEM Study 0910701
Version 1.0 | [figure not shown]
Hôpitaux de Toulouse |
|                    |                                                                   | 07/22/2016                                                                                                 |

Will be described:

- The number and percentage of recommendations proposed during MDTM1 that were followed by type of pathology;
- The number and percentage of pathologies that have been treated;
- The number and percentage of pathologies that have been resolved;
- The reasons why the recommendations were not followed;
- For diagnoses of dementia, the number and percentage of families and health care teams informed;
- The presence of new elements by type;
- The presence of new recommendations.

